#### Primary outcomes

##### Health-related quality of life

The Functional Assessment of Cancer Therapy-Prostate^42^ assesses men’s disease-specific quality of life across five domains: physical, social/family, emotional, functional well-being and PCa-specific concerns.^42^ The Assessment of Quality of Life (AQoL-8D) instrument is used to derive health utility scores and general HR-QoL among patients. This tool has increased measurement sensitivity to psychosocial elements of health compared with other instruments since it comprises five psychosocial dimensions (mental health, happiness, coping, relationships and self-worth) and three physical dimensions (independent living, pain and senses).^43^ The physical function subscale from the Medical Outcomes Study Short-Form-36 questionnaire will be used as an indicator of patient-related physical functioning QoL.^44^ We recently reported improvements in physical function in PCa patients with advanced disease and bone metastases following an exercise intervention using this measure, and in those on ADT with localised disease.^45^

##### Self-efficacy

The 11-item Cancer Survivorship Self-Efficacy Scale^46^ assesses self-efficacy to manage problems arising from cancer and its treatment specifically.

#### Secondary outcomes

##### Psychological distress

The Generalised Anxiety Disorder (GAD-7) scale^47^ and the depression subscale of the Patient Health Questionnaire (PHQ-9)^48^ will measure psychological distress. The seven-item GAD-7 scale screens for, and assesses the severity of, GAD in clinical practice and research. The nine-item PHQ-9 scale screens for, and assesses the severity of, depression and includes a specific item on suicidal ideation.

##### Insomnia

The Insomnia Severity Index is the worldwide standard, seven-item self-report measure to evaluate: (a) severity of sleep-onset, (b) sleep maintenance, (c) early morning awakening problems, (d) satisfaction with current sleep pattern, (e) interference with daily functioning, (f) noticeability of impairment attributed to the sleep problem and (g) level of distress caused by the sleep problem.^49^

##### Fatigue

The Multidimensional Fatigue Symptom Inventory-Short Form^50^ assesses general fatigue, physical fatigue, emotional fatigue, mental fatigue and vigour.

##### Physical activity/exercise

Godin-Shephard Leisure-Time Physical Activity Questionnaire,^51^ modified to include questions on resistance training, reflecting current best practice in exercise intervention trials for men with PCa,^52^ will assess physical activity.

#### Process evaluation

##### Programme acceptability

The AIM, IAM and FIM^33^ are a short self-reported assessment that is collected at T1 and T3 (patient participants) to determine patients’ experiences of the study from recruitment to 6 months postrecruitment. For patient participants, this is, included in the self-reported study assessments mailed to them at T1 and T3. The therapeutic alliance between patients in the intervention group and the nurses delivering the intervention will also be assessed by the 12-item WAI-SR.^41^ This will be included in the self-reported study assessments mailed to patient participants at T3.

All other study stakeholders receive the same assessments as an online survey when recruitment starts and ends to determine their study experience.

##### Interviews

Semistructured interviews exploring the constructs of the conceptual framework for implementation outcomes^25^ will be undertaken to determine effectiveness of the PCEssentials intervention delivery, and the potential for implementation of the intervention at scale. The interview question route informed by the literature is included in online supplemental file 1.

10.1136/bmjopen-2024-084412.supp1Supplementary data

### Statistical considerations and data analysis

Recent meta-analyses conclude that individually focused psychological interventions should produce improvements in psychological distress of at least a medium effect size (d=0.40) that will be clinically meaningful.^53^ To see an effect of this size or greater in our primary outcome, psychological distress at 12 months, with 80% power and alpha=0.05, we will require 99 participants in each group to complete the intervention. Assuming 15% attrition, we will recruit 236 patients to the study (118 patients per group).

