**Methods and analysis:**

This is an effectiveness-implementation hybrid (type 1) trial with participants randomised to one of two arms: (1) minimally enhanced usual care and (2) nurse-led prostate cancer survivorship essentials (PCEssentials) delivered over four tele-based sessions, with a booster session 5 months after session 1. Eligible participants are Australian men with prostate cancer commencing ADT and expected to be on ADT for a minimum of 12 months. Participants are followed up at 3, 6 and 12 months postrecruitment. Primary outcomes are HR-QoL and self-efficacy. Secondary outcomes are psychological distress, insomnia, fatigue and physical activity. A concurrent process evaluation with participants and study stakeholders will be undertaken to determine effectiveness of delivery of PCEssentials.

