### Aims

Aim 1: Determine the effectiveness of a nurse-led survivorship care intervention (PCEssentials), relative to usual care, for improving HR-QoL in men with PCa undergoing ADT.

Aim 2: Evaluate PCEssentials implementation strategies and outcomes, including cost-effectiveness of PCEssentials, with respect to usual care, as well as acceptability, adoption, appropriateness, feasibility, fidelity, penetration and sustainability.

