### Research outcomes and measurement tools

Previously validated and reliable patient-reported outcome assessments are administered by mail to men at four time points: baseline/recruitment (T1), 3 months (T2), 6 months (T3) and 12 months (T4) after recruitment. Primary outcomes are HR-QoL and self-efficacy. Secondary outcomes include global psychological distress, insomnia, fatigue and life satisfaction. Demographic moderators/disease variables (eg, cancer grade, stage, time since diagnosis, time since treatment) and a health service use diary are self-reported. Assessments are self-reports with pen and paper.

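### The only power statement is for psychological distress, which the protocol elsewhere makes secondary, so 80% power is not established for HR-QoL or self-efficacy, the declared primary outcomes

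*Protocol article*

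**What the plan says.** The protocol article assigns the primary outcome in several places, and they do not agree.

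- **Statistical considerations and data analysis** holds the only power statement: "To see an effect of this size or greater in our primary outcome, psychological distress at 12 months, with 80% power and alpha=0.05". It asks for 99 participants per group and, allowing 15% attrition, recruits 236 (118 per group). The d=0.40 is attributed to meta-analyses of psychological interventions for distress.
- **Abstract, Methods and analysis:** "Primary outcomes are HR-QoL and self-efficacy. Secondary outcomes are psychological distress, insomnia, fatigue and physical activity".
- **Research outcomes and measurement tools:** "Primary outcomes are HR-QoL and self-efficacy. Secondary outcomes include global psychological distress, insomnia, fatigue and life satisfaction".
- **Primary outcomes** describes the HR-QoL instruments (FACT-P, AQoL-8D and the SF-36 physical function subscale) and one self-efficacy scale.
- **Secondary outcomes** places GAD-7 and PHQ-9 there as the two scales that "will measure psychological distress".
- **Aims:** Aim 1 concerns the effectiveness of the intervention "for improving HR-QoL in men with PCa undergoing ADT". It mentions neither self-efficacy nor distress.
- **Primary hypothesis** names cost-effectiveness, then lists HR-QoL, self-efficacy, distress, and sleep and fatigue, at 3, 6 and 12 months. Distress is third in that list, and no single endpoint is picked out.

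**The concern.** A power statement tells the reader what difference the trial was planned to detect in the outcome on which its conclusion rests. Here it is attached to an outcome that every section classifying outcomes calls secondary. Replacing one word would not repair it, because the justification for 0.40 is also specific to distress. Nothing in the document says what difference in HR-QoL or self-efficacy is expected or worth detecting.

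Two things are at stake. First, an HR-QoL or self-efficacy result cannot be set against a planned detectable effect for that outcome. Second, the text contains two statements of what is primary, so a later report on either could cite the protocol in support.

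**Working it through.** **Inputs.** From the sample-size paragraph: d=0.40, alpha 0.05, power 80%, 99 per group, 15% attrition, 236 in total. Sidedness is not stated.

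**Step 1: reproduce the plan's figure.**

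- n per group = 2(z₁₋α/₂ + z₁₋β)² / d² = 2(1.96 + 0.8416)² / 0.40² = 98.1, rounded up to 99. A t-based calculation gives 99.08. A one-sided test would need only 78, so the stated figure is two-sided.
- Attrition: 99/0.85 = 116.5, so 117 per group and 234 in total. Starting from 100, 100/0.85 = 117.6, so 118 per group and 236 in total. Conversely, 118 × 0.85 = 100.3.

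The stated 99 and 236 are reproduced. The fault is not in the calculation.

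**Step 2: what carries over to the declared primary outcomes.** Because d is standardised, the same 99 per group give about 80% power for HR-QoL or self-efficacy if two conditions hold: d=0.40 also applies there, and each outcome is tested at the full two-sided 0.05. The document states neither.

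**Step 3: illustrate the dependence on d.** Power ≈ Φ(d√(n/2) − 1.96), with n=99 and √(99/2) = 7.036. The d values other than 0.40 are assumptions.

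| d | d√(n/2) | Power at two-sided 0.05 |
|---|---|---|
| 0.25 | 1.759 | 42% |
| 0.30 | 2.111 | 56% |
| 0.35 | 2.462 | 69% |
| 0.40 | 2.814 | 80% |
| 0.50 | 3.518 | 94% |

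These are unadjusted two-group comparisons at one time point.

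**Step 4: illustrate the dependence on alpha.** If alpha were split equally over two primary outcomes (0.025 each, an assumption), the critical value is 2.241. At d=0.40 power is Φ(2.814 − 2.241) = Φ(0.573), about 72% (71% with a t-test). Reaching 80% would then take 119 per group with data: 119/0.85 = 140 per group, or 280 in total.

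**The case against.** The strongest reply is that the grid in Step 3 proves no shortfall. Nothing in the document suggests that effects on HR-QoL or self-efficacy are smaller than 0.40. They could be larger, and at 0.50 power is 94%. The grid also ignores the planned analysis, which fits mixed models to change from baseline with repeated measures. With adjustment for baseline and an assumed baseline-to-12-month correlation of 0.5, d is divided by √(1 − 0.25) = 0.866. Power at 0.35 then becomes about 81% rather than 69%, and at 0.30 about 68% rather than 56%. A pure change-score analysis would gain less. This objection stands in full. A reader might infer that the trial is underpowered for HR-QoL, but the document does not support that.

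A second reply is that the abstract and outcome sections agree with each other, so the sample-size phrase may be a drafting slip. It may be, but the effect size in the same paragraph is also tied to distress, so the paragraph would still lack a basis for the declared outcomes. A reader might also infer that the sponsor intends to choose the primary outcome after seeing results. The document gives no sign of that, and the trial is registered, with a record not seen here. A null HR-QoL result could also still be read from its confidence interval.

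A third reply is that an analysis plan or fuller protocol may give more detail. That would excuse an omission, but it cannot make two conflicting statements in the current text both true. Two smaller matters carry no weight here: how the two distress scales would be combined, and the paragraph's reference to finishing the intervention rather than providing 12-month data.

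**Conclusion.** The point holds as an internal contradiction that must be resolved. The trial is sized on distress at 12 months under the label of primary outcome, while the abstract and outcome sections make HR-QoL and self-efficacy primary. The stated 80% power is correct for a standardised difference of 0.40 in one outcome tested at two-sided 0.05. It is not established for either declared primary outcome. How far their power would differ cannot be determined from the document: it depends on an effect size that is not given and on how alpha is handled across two outcomes. The figures of 42% to 94% over d of 0.25 to 0.50, and about 72% at d=0.40 under an equal alpha split, are illustrations under those assumptions.

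**What to change.** Keep N=236 and, before unblinding, reconcile the abstract, the primary hypothesis, the outcome sections and the sample-size paragraph on what is primary.

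- **If HR-QoL and self-efficacy stay primary:** name one of the three HR-QoL instruments and the time point, and state how alpha is handled across the two outcomes. Restate the power of each with 99 men per group providing 12-month data: about 80% at d=0.40 if each is tested at two-sided 0.05, or about 72% if alpha is split to 0.025 each. Say that 0.40 is carried over from distress trials, and show power over a range of d, labelled as an unadjusted illustration.
- **If distress is truly primary:** change the abstract and outcome sections to match, and name GAD-7 or PHQ-9 as the scale that the power refers to.

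The cost is rewording, mainly of one paragraph, with no extra patients. The downside is that the stated power may look less favourable, particularly if alpha is split.

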#### Intervention effectiveness

The study is a two-arm randomised controlled trial with repeated assessments across time and with continuous primary outcome variables. Recruitment bias will be assessed by comparing sociodemographic and clinical variables for consenters with non-consenters using t-tests (or Mann-Whitney U tests) for continuous variables and χ^2^ tests for categorical variables. Possible differential attrition will be assessed by comparing baseline characteristics of drop-outs and continuing participants using t-tests (or Mann-Whitney U tests if appropriate) for continuous variables and χ^2^ tests for categorical variables. Intention-to-treat analyses will be conducted. Between-group mean differences in change from baseline outcome scores at 3, 6 and 12 months will be analysed by fitting mixed effects regression models. Intervention (intervention/usual care) will be included as the main effect. Indicators for participants will be included as a random effect to account for the non-independence of repeated observations from the same individual. Sensitivity analysis will assess the effects of attrition. Mixed effects models with maximum likelihood estimation minimise bias that may arise from ignoring missing observations, and use all available data, thereby maximising statistical power to detect effects. The mean and 95% CI will be calculated for satisfaction with the intervention. Missing data will be examined for patterns of missingness and addressed with the appropriate multiple imputation methods, if required. The investigator team includes a dedicated biostatistician who will undertake analyses.

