### Randomisation

Randomisation to study group condition occurs following receipt of baseline assessments (figure 2). Randomisation occurs in varying block sizes of 4, 6 and 8 (to ensure an unpredictable allocation sequence with equal numbers of men in each treatment group at the completion of each block) with no stratification factors. The randomisation sequence is undertaken by the project manager and concealed from investigators. Project staff tracking assessments (data analysts) will be blinded to condition.

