#### Cost–utility analysis

A cost–utility analysis of the intervention relative to minimally enhanced usual care from both healthcare payer and societal perspectives will be conducted alongside the PCEssentials trial. Costs will be obtained by identifying, measuring and valuing the health resources used. At baseline, participants are given a health service use diary to record direct health resources utilised (eg, general practitioner visits, treatments and hospitalisations), as well as out-of-pocket expenses and indirect costs (eg, productivity loss). The diaries will also be collected during the T2, T3 and T4 assessments. Healthcare resources will be valued using unit prices from standard costing resources such as the Medicare Benefits Schedule and relevant Australian award wages. Quality-adjusted life-years (QALYs) gained will be estimated, which is a measure of a patient’s life expectancy, weighted by his HR-QoL (ie, utility score) measured using the AQoL-8D at baseline, 3, 6 and 12 months. A multivariate generalised linear model will be used to adjust for differences in baseline AQoL-8D scores, demographics and disease classifications. The incremental cost-effectiveness ratio (ICER) will be calculated, which is the difference in mean costs divided by the difference in mean QALYs. Non-parametric bootstrapping will be used to characterise uncertainty around the ICER. If the intervention appears to be cost-effective, we will calculate the expected value of implementation, which is the net monetary benefit of the intervention (ie, monetary benefits—costs) multiplied by the population of PCa patients expected to benefit from the intervention and adjusted by various patients’ adherence and clinicians’ uptake rates. Uptake rates will be obtained from a formal elicitation exercise and will inform a Bass model to forecast diffusion (ie, implementation over time).^56^

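### The effectiveness analysis compares change from baseline with no baseline covariate named; it is unbiased, but adjusting for the baseline score would be more precise at no cost

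*Protocol article*

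**What the plan says.** The Intervention effectiveness section fixes the analysed quantity: "Between-group mean differences in change from baseline outcome scores at 3, 6 and 12 months will be analysed by fitting mixed effects regression models". It names intervention as the main effect and participant as a random effect. It does not mention the baseline score as a covariate. Visit and group-by-visit are not named either.

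The sample size paragraph under Statistical considerations and data analysis is written for a 12-month comparison with a standardised effect of 0.40. It refers to "our primary outcome, psychological distress at 12 months, with 80% power and alpha=0.05" and concludes that "we will require 99 participants in each group to complete the intervention". It gives no baseline to follow-up correlation and does not say whether 0.40 is in SDs of the raw score or of the change score.

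Under Research outcomes and measurement tools, the primary outcomes are HR-QoL and self-efficacy, and psychological distress is secondary. The Randomisation section has baseline questionnaires returned before allocation, so every randomised man should have a baseline assessment.

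**The concern.** A change score uses the baseline but fixes its slope at 1. When baseline and follow-up are imperfectly correlated and have similar variances, the best slope is r, which is less than 1. Subtracting the whole baseline then adds noise, and chance baseline differences between the groups are over-corrected in any single trial. Estimating the slope removes that noise.

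Precision is what is at stake. Wider confidence intervals, and for some correlations lower power, would be accepted although the data needed to avoid them are already collected. The same section gives maximising power as a reason for choosing mixed models, so the improvement serves the plan's own aim.

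**Working it through.** **Inputs.** From the sample size paragraph: d = 0.40, 80% power, alpha 0.05, 99 completers per group, 15% attrition, 118 per group recruited. Sidedness is not stated; two-sided is taken because it reproduces 99 (one-sided gives 78). The correlation r is not in the document, so a range of 0.2 to 0.8 is assumed. Baseline and follow-up variances are assumed equal and set to 1.

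**Step 1: reproduce the stated figure.** n per group = 2(1.960 + 0.842)² / 0.40² = 98.1, rounded up to 99. This matches. Power at 99 is Φ(0.40 × √(99/2) − 1.960) = Φ(0.854) = 80.4%. For attrition, 99/0.85 = 116.5, or 117 per group, close to the stated 118. The calculation is a plain two-sample comparison in which no baseline correlation appears.

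**Step 2: variances.**
- Change score: 2(1 − r)
- Baseline-adjusted: 1 − r²
- Ratio, adjusted to change: (1 − r²) / [2(1 − r)] = (1 + r)/2, below 1 for every r below 1

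**Step 3: power at 12 months, 99 per group, d in raw-score SDs.** Power = Φ(0.40/√variance × √(99/2) − 1.960). At r = 0.3 the change score gives 0.40/√1.4 × 7.036 − 1.960 = 0.418, so 66.2%. The adjusted analysis gives 0.40/√0.91 × 7.036 − 1.960 = 0.990, so 83.9%.

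| r | Variance ratio | Power, change | Power, adjusted | n per group for 80%, change | n per group for 80%, adjusted |
|---|---|---|---|---|---|
| 0.2 | 0.60 | 60.4% | 81.9% | 157 | 95 |
| 0.3 | 0.65 | 66.2% | 83.9% | 138 | 90 |
| 0.4 | 0.70 | 72.9% | 86.7% | 118 | 83 |
| 0.5 | 0.75 | 80.4% | 90.1% | 99 | 74 |
| 0.6 | 0.80 | 88.2% | 94.0% | 79 | 63 |
| 0.7 | 0.85 | 95.3% | 97.6% | 59 | 51 |
| 0.8 | 0.90 | 99.4% | 99.7% | 40 | 36 |

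The change score matches the plain two-sample calculation exactly when 2(1 − r) = 1, that is r = 0.5. Below that its power is under 80%; above it, over 80%.

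**Step 4: two other readings.**
- *One effect averaged over the three visits, all correlations equal to r.* The change-score variance is (1 + 2r)/3 + 1 − 2r = (4/3)(1 − r), which equals 1 at r = 0.25. Power is 77.8% at r = 0.2 and 83.0% at r = 0.3. The adjusted variance is (1 + 2r)/3 − r², which gives 99.1% and 98.8%.
- *d = 0.40 standardised on the change-score SD.* The change-score analysis has 80.4% power whatever r is. Adjustment raises this to 93.7% at r = 0.3, 90.1% at r = 0.5 and 86.3% at r = 0.7.

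**The case against.** The strongest reply is that the inefficient analysis is inferred from silence. The article is condensed and nowhere excludes a baseline covariate. The listed terms cannot be complete, since estimates at three visits need visit and group-by-visit terms. The wording is also compatible with the fix: once the baseline score is in a linear model, taking the change or the follow-up score as response gives the same treatment estimate, and a constrained longitudinal model also estimates a difference in change. All of this stands, and a fuller document may already add the covariate. But the article does specify the analysed quantity and the fixed effect. Followed as written, it gives the less precise estimate. Treating baseline as one of the repeated outcomes with unconstrained group means does not rescue it: with complete data that yields the same difference in change.

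A reader might go further in three ways that the document does not support.

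- *That the plan contradicts itself*, because the cost–utility section says "A multivariate generalised linear model will be used to adjust for differences in baseline AQoL-8D scores, demographics and disease classifications". That model serves QALYs, which accumulate utility over time and have no baseline subtracted. They are a different quantity handled differently.
- *That randomisation "with no stratification factors" adds a further harm.* The variance 2(1 − r) already includes chance baseline imbalance, so this would count it twice.
- *That baseline data are wasted.* They are used, through subtraction, but inefficiently.

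**Conclusion.** The point holds as one of efficiency, not validity. As written, the analysis is unbiased under randomisation but less precise than baseline adjustment at every r below 1, assuming equal variances. The variance saving is 35% at r = 0.3, 25% at r = 0.5 and 15% at r = 0.7.

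A reader might infer that the trial misses its stated 80% power on its primary outcomes. The document does not support that. The 80% is stated for psychological distress at 12 months, and no power is stated for HR-QoL or self-efficacy. For distress, a shortfall needs d in raw-score SDs and r below 0.5, or below about 0.25 for an effect averaged over visits with equal correlations. There is no shortfall if d is on the change-score SD. The article gives neither r nor the scale of d. The 99 per group itself reproduces and is not in error.

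The change should be made because it gains precision for nothing, whichever reading applies.

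**What to change.** State in the effectiveness section that the 3-, 6- and 12-month scores (or changes) are modelled with the same scale's baseline score, group, visit, group-by-visit and baseline-by-visit as fixed effects. A constrained longitudinal model with a common baseline mean in both groups is an equally good choice. Apply the chosen model to every outcome and report the adjusted difference as the main estimate. If a fuller analysis plan already includes the baseline covariate, one sentence saying so settles the point.

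The cost is a wording change. Baseline assessments are already collected before randomisation, so no extra data, visits or patients are needed.

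### A participant random effect alone implies equal correlation between all visits; if correlation falls over time, the 12-month standard error is too small and the 3-month one too large

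*Protocol article*

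**What the plan says.** The section 'Intervention effectiveness' sets visit-specific comparisons: "Between-group mean differences in change from baseline outcome scores at 3, 6 and 12 months will be analysed by fitting mixed effects regression models". Intervention is the only fixed effect it names. For dependence within a man it says: "Indicators for participants will be included as a random effect to account for the non-independence of repeated observations from the same individual". It mentions no random slope, no residual covariance structure and no robust standard error. Its sensitivity analysis concerns attrition.

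The visits are unequally spaced. 'Research outcomes and measurement tools' gives them as "baseline/recruitment (T1), 3 months (T2), 6 months (T3) and 12 months (T4) after recruitment". The sample size paragraph refers to the last of these: "psychological distress at 12 months, with 80% power and alpha=0.05".

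**The concern.** Read plainly, the dependence sentence describes a random intercept with independent residuals. That model gives baseline and 3 months the same correlation as baseline and 12 months, and so one common variance for all three changes from baseline. Repeated scores on the same man may well be less alike over 12 months than over 3. In that case the model averages over the lags: it borrows precision from the short lags for the 12-month contrast and takes it away from the 3-month contrast.

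The 12-month comparison is the one the trial is sized for, and it is where the error would be understated. Its 5% test would reject too often and its 95% confidence interval would cover too seldom. The 3-month test would be conservative and lose power.

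**Working it through.** **The plan's own figure.** Inputs from the sample size paragraph: d = 0.40, 80% power, alpha 0.05 (taken as two-sided), 15% attrition. Per arm, n = 2(1.960 + 0.842)²/0.40² = 98.1, so 99, as stated. Then 99/0.85 = 116.5 and 100/0.85 = 117.6, so 118 per arm (236 in all) is adequate. This calculation compares two groups at one time and uses no correlation between visits, so the point below does not touch it.

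**Formulas.** Take constant SD = 1, n = 118 per arm, complete data, and a group-by-visit model on the four visits.
- True variance of the difference in change at visit t: 4(1 − ρ₀ₜ)/n, where ρ₀ₜ is the correlation of visit t with baseline.
- Variance that the random-intercept model reports at every visit: 4(1 − ρ̄)/n, where ρ̄ is the mean of the six pairwise correlations.
- Ratio of model to true standard error: r = √[(1 − ρ̄)/(1 − ρ₀ₜ)].
- Actual two-sided type I error: 2[1 − Φ(1.96 r)].

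**One worked case (assumed correlations).** Correlations of 0.70, 0.62, 0.56 and 0.50 at lags of 3, 6, 9 and 12 months. The six pairs are 0.70, 0.62, 0.50, 0.70, 0.56 and 0.62, with mean ρ̄ = 3.70/6 = 0.617.
- 12 months: r = √(0.383/0.50) = 0.876, so the standard error is 12% too small. Type I error is 8.6%, and the 95% interval covers about 91.4%.
- 6 months: r = √(0.383/0.38) = 1.00; type I error 4.9%.
- 3 months: r = √(0.383/0.30) = 1.13; type I error 2.7%.

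**Range over other assumed patterns, same formulas.**

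| Correlation, 3-month to 12-month lag | r at 3 months | Type I error | r at 12 months | Type I error |
|---|---|---|---|---|
| Flat at 0.60 | 1.00 | 5.0% | 1.00 | 5.0% |
| Linear, 0.65 to 0.55 | 1.05 | 3.9% | 0.93 | 6.8% |
| Linear, 0.75 to 0.45 | 1.21 | 1.8% | 0.82 | 11.0% |
| Linear, 0.80 to 0.40 | 1.33 | 0.9% | 0.77 | 13.1% |
| Autoregressive, 0.80 per 3 months | 1.35 | 0.8% | 0.79 | 12.3% |
| Autoregressive, 0.90 per 3 months | 1.41 | 0.6% | 0.76 | 13.6% |

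**Other forms of the model.** The calculation was repeated for constrained-baseline, change-score and two baseline-adjusted versions, with and without 15% dropout completely at random. In every falling-correlation pattern r was 0.75 to 0.95 at 12 months, 0.98 to 1.07 at 6 months and 1.04 to 1.45 at 3 months. At the extremes, r = 0.95 gives 6.3% and r = 0.75 gives 14.2% at 12 months; r = 1.04 gives 4.2% and r = 1.45 gives 0.4% at 3 months.

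**Simulation check.** In 300 simulated null trials (100 per arm, linear 0.75 to 0.45), the fitted mixed model reported a standard error of 0.121. The empirical values were 0.100 at 3 months and 0.149 at 12 months. Rejection rates were 0.7% and 12.3%.

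**The case against.** The strongest objection is that this is a condensed article. Residual covariance and the type of standard error are commonly left to an analysis plan, which is not shown here. The sentence says that a participant effect will be included. It does not say that nothing else will be, and such an effect can sit beside structured residuals or sandwich standard errors. A reader might infer that the plan fixes compound symmetry and rules out any alternative; the text does not go that far. What remains is that the article does state how non-independence is to be handled, and an analyst who follows it by default gets the model examined above.

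Second, no visit term or arm-by-visit term is written. If only a pooled intervention effect were fitted, there would be no 12-month standard error, and the pooled one was correct (ratio 1.00). But that model would not deliver the visit-specific differences that the same paragraph promises.

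Third, the size rests on assumptions. A reader might infer a 12-month error of at least 8%. The documents do not support that: mild decay gives 6.8%. Adjusting for baseline while keeping the random intercept lowers the worked case from 8.6% to about 7.4%, and the mild case to 6.2%. If the SD also fell linearly from 1.0 to 0.8 by 12 months, the baseline-adjusted worked case would be about 5.0%. These limits stand, and the conclusion is worded to fit them.

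A reader might also infer that the trial is too small or its estimates biased. Neither follows: 236 does not depend on these correlations, and with complete data the treatment estimates are unbiased.

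**Conclusion.** The point holds conditionally. It needs three things: the dependence sentence read as a random intercept with independent residuals and model-based standard errors; correlation that falls with time between visits; and roughly constant variance. The documents supply no figures for the last two. Given all three, the direction is the same in every pattern and visit-specific model tried.

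The 12-month standard error is then about 5 to 25% too small, with type I error of about 6 to 14% against a nominal 5%. At 3 months type I error is about 0.5 to 4%, and the 6-month test is close to right. If correlation is flat, nothing is wrong. This is a cheap improvement to a stated method, not a defect that invalidates the design.

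**What to change.** Specify a mixed model for repeated measures with arm, visit as a category, arm-by-visit and baseline score, and an unstructured within-participant covariance matrix. Name the 12-month difference from this model as the 12-month result. If the model does not converge, fall back on the random intercept with robust (sandwich) standard errors.

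The change is one of wording, and neither the data collected nor the sample size alters. The price is a few more covariance parameters: six for three follow-up visits with baseline as a covariate (ten if baseline is kept as a fourth outcome), against two for a random intercept. With 236 men that is easily supported. The convergence rule has to be written before the data are analysed.
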